#### SAS

The anxiety level of NCNP patients will be measured by Zung Self-Rating Anxiety Scale (SAS) [47]. Twenty questions are divided into 4 groups: cognitive, autonomic, motor, and central nervous system symptoms. Each section is scored on four levels of anxiety intensity from “1” not at all to “4” very much and with a sum score between 20 and 80. A higher total score indicates a more severe anxiety level. The total raw scores range from 20 to 80. The raw score consequently needs to be converted to an “Anxiety Index.” The primary scores should be interpreted into the Anxiety Index. The clinical interpretation of one’s level of anxiety is as follows: 20–44, normal range; 45–59, mild to moderate; 60–74, marked to severe lever; and 75–80 extreme anxiety level.

#### Tissue hardness

Tissue hardness is measured by a digital algometer (OE-220, ITO, Tokyo, Japan) The measurement has been used to test the tissue hardness in previous study [48–50]. The measuring point is placed between C7 and acromion at the middle point of the upper trapezius muscle. The researcher puts the meter on the measuring point perpendicularly and push the force slowly. When hearing the deep sound, the researcher should stop pushing and read the number. To standardize the speed of using this application, the researchers responsible for this measurement will practice 1 week before the study. They must explain the measurement by demonstrating at the thenar region of the hand. Three soft tissue measurements will be preformed at each point with an interval of 30 s between the two measurements; the mean of three measurements will be recorded.

#### Active range of motion (AROM)

Cervical active range of motion is measure by Spain ScanTM SH-105 (Ad-Or Medical Technologies Ltd., Israel). The validity and reproducibility of this measurement have been proved by many researchers [51, 52]. SH-105 is composed of a goniometer and a computer. The data will be transmitted by Bluetooth. The patient will be seated with a straight back leaning against the back of a chair. The goniometer will be placed on the center of the cranial. The researcher switches the mode and long press the “start/end” button. When hearing the prompt sounds, the patient will be asked to flex forward to the limit. The patient will be instructed to stop at the point where pain symptoms preform. The research press the “start/end” button again, and the computer will automatically record the data. Each movement (flexion-extension, lateral flexion as well as rotation) will be measured in this way three times. The mean of each movement will be recorded.

### Safety evaluation

The safety of patients will be monitored in every visit. Two attending physicians and two responsible spine care specialists will be responsible for the collaboration and guidance of clinicians during each clinical trial and implementation. The two chief spinal surgeons constitute the endpoints Adjudication Committee, which is responsible for the overall supervision of the clinical trials. The AES in trial are changes in pain, syncope, vertigo, and disability. For any AES, no matter if it is or not caused by intervention, the treatment will be stopped immediately. The patient should take any medical aids to alleviate symptoms. The adverse events should be reported to the relevant responsible unit and the ethics committee in time. If the adverse events are confirmed to be related to the study, the regional Ethics Review Committee of Yueyang Integrated Traditional Chinese and Western Medicine Hospital affiliated to Shanghai University of Traditional Chinese Medicine has the right to suspend the study. If an adverse event occurs during the clinical trial, medical experts will be engaged to assess and investigate the actual cause, and medical and financial compensation will be made to participants.

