**Fig. 1 Fig1:**
[figure not shown]
Trial flow chart. Diagram demonstrating the randomized controlled trial protocol. A total of 102 eligible NCNP patients will be randomly allocated to the group of Tuina and Tuina combined with Yijinjing in a 1:1 ratio. The dropout will be analyzed by ITT analysis

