### Dropout criteria

Participants who do not complete the clinical protocol for the following reasons should be considered as dropped out:
The patient quits (poor efficacy or adverse reactions)Loss to follow-upResearchers remove the patient (poor compliance or serious adverse events)

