### Interventions

The Tuina protocol used in this trial is the same as those used in our previous studies [38, 39]. It includes soft tissue manipulation and spinal manipulation, such as rolling, pressing, and tapping. Yijinjng for NCNP patients was designed on the basis of the textbook which has been used for teaching students in the universities of TCM [40, 41].

Participants in the Tuina group or the Yijinjng combined with Tuina group will receive Tuina treatment 3 times a week for 8 weeks. The treatment room will be controlled at 23–25° to ensure that the participants feel comfortable. The participants will be asked to rest for 15 min before Tuina treatment. They will be advised to lie in the prone position during the treatment. The intensity level of Tuina is based on physical examination and the therapist’s clinical experience, as well as after careful communication with each study participant. Tuina treatment will last for 25 min.

The participants who are in the Yijinjng combined with Tuina group will practice Yijinjing 3 times a week for 8 weeks. The patients will be assembled once a week for practicing Yijinjing together. The Yijinjing teacher will teach them how to practice Yijinjing. The teacher will also correct the wrong movement of patients. The patients will practice Yijnjing another two times per week at home. A digital video disk about the movements of Yijinjing in this trial will be provided to the participants. They can review the movements at home easily. The participants are asked to film themselves and sent it to the teacher by email or WeChat. The teacher will examine the participants’ video carefully and give the patients some advice about practicing Yijinjing. Yijinjing treatment will last for 30 min.

VAS, NDI, SAS, soft tissue hardness, and AROM will be assessed at the baseline and 4, 8, and 12 weeks.

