### Statistical analysis

All statistical analyses will be performed with the SPSS software (SPSS, version 24.0, SPSS Inc., Chicago, IL, USA) by statisticians who are independent of the research team and blinded to the group allocation. Data analysis will be based on the intention-to-treat (ITT) principles. The statistical significance was accepted for values of *p* < 0.05. Participants who fail to complete the study will be treated as having no change from baseline at all times. Descriptive statistics will be used to compare demographic and baseline information and evaluate the credibility of the groups. The normality of data will be tested by the Kolmogorov-Smirnov test. Parametric statistics (Tukey test) or non-parametric statistics (Wilcoxon rank sum test) will be used for the within- and between-group according to the results of homogeneity and normality analysis. If the data does not conform to a normal distribution, a covariance analysis will be used. The efficacy will be measured at four time points. A repeated measures analysis of variance will be conducted to analyze dependent variables (from baseline and follow-up). The Bonferroni and Dunn tests will be used for multiple comparisons. The intra-group comparison (comparison between baseline and follow-up) will be tested by a two-sided paired *t* test. The difference of categorical variables (VAS, NDI, SAS, PPT, AROM) and adverse effects between the groups will be analyzed by using The chi-square test or Fisher’s exact test. All numerical data will be presented as the mean ± SD, and categorical variables will be described with percentages (%). If it is necessary, post hoc analyses will be performed. The confidence interval will be established at 95% and the significance level at 0.05.

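### The no-change rule for non-completers is not limited to missing visits, so it can overwrite worsening already recorded in patients who leave because of adverse events

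*Protocol article*

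**What the plan says.** Four parts of the protocol article bear on this.

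- **Dropout criteria** defines the group: "Participants who do not complete the clinical protocol for the following reasons should be considered as dropped out". The first listed reason reads "The patient quits (poor efficacy or adverse reactions"; the others are loss to follow-up and removal by the researchers for poor compliance or serious adverse events. The test is whether the clinical protocol was completed, not whether a visit was missed.
- **Statistical analysis** declares "Data analysis will be based on the intention-to-treat (ITT) principles" and, in the same paragraph, "Participants who fail to complete the study will be treated as having no change from baseline at all times". The Fig. 1 caption adds "The dropout will be analyzed by ITT analysis".
- **Safety evaluation** lists the adverse events, "The AES in trial are changes in pain, syncope, vertigo, and disability", and the action: "For any AES, no matter if it is or not caused by intervention, the treatment will be stopped immediately". Pain is what the primary VAS measures, and disability is what the secondary NDI measures.
- **Interventions** sets the assessments without exception: "VAS, NDI, SAS, soft tissue hardness, and AROM will be assessed at the baseline and 4, 8, and 12 weeks".

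**The concern.** A no-change rule is usually offered as a cautious way to fill a gap: a patient who leaves gets no credit for improvement that nobody saw. Here the wording goes further. It applies at every time point and does not ask whether a score exists. A patient who was measurably worse at week 4 and then left over an adverse reaction could enter the analysis as unchanged at weeks 4, 8 and 12.

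For such a patient the rule is not cautious, because it makes the arm look better than its data. Discarding a recorded outcome because of something that happened after randomisation also conflicts with the intention-to-treat principle stated beside it. The scores at risk belong to the patients most informative about harm, in a trial whose Tuina protocol includes an abrupt manipulation of the neck.

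**Working it through.** **1. The plan's own figures.** Sample size calculation gives means of 5.5 and 4.7 cm, SD 1.3, two-sided alpha 0.05 and power 80%.

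- n = 2 × (1.96 + 0.84)² × 1.3² / (4.7 − 5.5)² = 26.50 / 0.64 = 41.4, rounded up to 42 per group, as stated.
- 42 × 1.2 = 50.4, rounded up to 51 per group, as stated.

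Only two of these figures are used below: 51 as the number analysed per arm under intention to treat, and 5.5 − 4.7 = 0.8 cm as a yardstick. The textual point depends on neither.

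**2. The rules applied to four patients.**

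- *Quits over an adverse reaction after a worse week 4 score.* A dropout by the listed reason. If dropouts are non-completers, the recorded week 4 worsening becomes zero.
- *Removed for a serious adverse event after a worse week 4 score.* The same result.
- *Leaves before any post-baseline visit.* No score exists to overwrite; the rule only fills gaps.
- *Treatment stopped for a non-serious event, patient neither quits nor is removed.* Not on the dropout list. The assessment schedule still applies, so observed scores may well be used. The article does not say.

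The step from not completing the clinical protocol (Dropout criteria) to failing to complete the study (Statistical analysis) is an inference. It is a natural one, because the article gives no other specific rule for dropouts' scores, but it remains a condition of the conclusion.

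**3. Size, for illustration.** Suppose k patients in an arm of 51 have a recorded worsening of w cm that is set to zero. The arm mean change then looks better by k × w / 51. The article gives neither k nor w, so both are assumptions.

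| k | w (cm) | Shift in arm mean (cm) | Share of 0.8 cm |
|---|---|---|---|
| 1 | 1 | 1/51 = 0.020 | 2.5% |
| 2 | 2 | 4/51 = 0.078 | 9.8% |
| 3 | 3 | 9/51 = 0.176 | 22.1% |

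**4. Effect on the comparison.** The between-arm error is the difference between the two arms' shifts: (k₁w₁ − k₂w₂)/51. With equal exits and equal worsening it is zero, however many patients are overwritten. The table therefore shows an error in the comparison only if k is read as a net excess in one arm.

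**The case against.** The best defence is that the article can be read sensibly. It declares intention to treat twice, schedules every assessment without exception, and may intend the no-change rule only for patients who are no longer there to be measured. On that reading nothing observed is lost. This is fair and is why the conclusion is conditional. But the rule's own words say otherwise, and two readings that lead to different primary data should not be left open.

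It is also true that both arms receive the same Tuina, so exits caused by manipulation should largely balance. Only the combined arm adds Yijinjing, so unequal exits are possible, but nothing in the article shows that they will occur or in which arm.

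Three stronger readings are tempting and are not supported.

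- *A reader might infer that the stopping rule in Safety evaluation itself sends patients into the no-change rule.* It does not. It stops treatment, possibly only the session, and withdraws nobody from the study; a non-serious stop is not among the dropout reasons.
- *A reader might infer that the adverse-event definition is defective because it has no grading and could capture the soreness sought during acupoint pressing.* Grading and expected reactions are details that a condensed article commonly leaves to the full protocol. The article treats that sensation as a guide to force, not as an adverse event.
- *A reader might turn the last row of the table into an inflated false-positive rate.* That row is 0.69 standard errors (0.176 / 0.257, with 1.3 × √(2/51) = 0.257 cm), and as a fixed shift it would give about 10.5% rejection. But this needs three net extra exits in one arm, each 3 cm worse, while other patients in that arm exactly offset them so that the true means stay equal. If outcomes and exits are distributed alike in both arms, the rule acts alike on both and the test stays at about 5%.

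**Conclusion.** The point holds in a limited form. As written, the no-change rule can replace recorded VAS and NDI worsening in patients who quit over adverse reactions or are removed for serious adverse events, contrary to the declared intention-to-treat principle. This rests on one assumption: that dropouts are treated as participants who failed to complete the study.

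The established consequence is that harm within an arm can be hidden. Bias in the comparison is possible but not shown. It needs a difference between arms in such exits or in their worsening, and the article supplies no rate, size or direction for either. A single patient 1 cm worse shifts an arm mean by about 0.02 cm, and balanced exits give no net error. The case for correcting the wording is that it leaves the primary data open to two readings and that the correction is cheap, not that a large bias is expected.

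**What to change.** Two statements are needed.

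- **Dropout criteria:** stopping treatment, including a stop for an adverse event under Safety evaluation, does not end outcome assessment. The patient is still invited to the week 4, 8 and 12 visits unless consent to follow-up is withdrawn.
- **Statistical analysis:** every observed score is analysed as recorded, and the no-change rule applies only to values that are actually missing.

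Immediate safety stops stay as they are. The cost is a few sentences of protocol text and a matching case report form instruction; the visits already exist. The downside is that Safety evaluation provides for medical aid after an event, so some observed scores will reflect that aid as well as the assigned treatment. The wording should be settled before the data are locked.

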**Methods/design:**

A randomized controlled trial in which 102 patients with non-specific chronic neck pain will be recruited and randomly allocated to either the Tuina group or the Yijinjng combined with Tuina group in a 1:1 ratio. The interventions for both groups will be carried out three times a week for 8 weeks. The patients in the two groups will receive follow-up 1 month after the intervention. The primary outcome will be the changes in the visual analog scale (VAS). Secondary outcomes will be measured by the Neck Disability Index (NDI), Self-Rating Anxiety Scale (SAS), and Tissue Hardness and Active Range of Motion (AROM). The data will be analyzed at the baseline, 4 weeks during the intervention, at the end of the intervention, and 1 month after the intervention. The significance level sets as 5%. The safety of interventions will be evaluated after each treatment session.

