### Follow-up

To evaluate the long-term efficacy and safety of the intervention, we will follow up the patients after treatments for 1 month. During this period, patients would not receive any treatment. No researcher will supervise them. At the end of the week, the outcome assessor will make a contract with patients by WeChat, telephone, e-mail, etc. They will be asked to come to the reception room and fill in the relevant scales above. Tissue hardness and AROM will be measured at the same time.

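### The adverse-event definition is worded as a closed list of four items, so read as written some neurological signs and falls are not adverse events

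*Protocol article*

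**What the plan says.** The definition is one sentence in the Safety evaluation section of the protocol article: "The AES in trial are changes in pain, syncope, vertigo, and disability". Duties follow from it in the same section. On stopping: "For any AES, no matter if it is or not caused by intervention, the treatment will be stopped immediately". On reporting: "The adverse events should be reported to the relevant responsible unit and the ethics committee in time". The section then provides for experts to investigate the cause and for medical and financial compensation. The Statistical analysis section says that "adverse effects between the groups will be analyzed by using The chi-square test" or Fisher's exact test, without saying what an adverse effect is.

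Safety appears in several other places:
- The abstract says "The safety of interventions will be evaluated after each treatment session".
- Dropout criteria name adverse reactions as a reason for quitting ("The patient quits (poor efficacy or adverse reactions") and serious adverse events as a reason for removal.
- Comprehensive suspension criteria allow the trial to be halted for a significant safety problem.
- Data collection and management puts adverse events and safety evaluations on the CRF.
- Quality control has independent reviewers check 10% of case reports, including abnormal safety indicators.
- Follow-up gives the month after treatment a safety purpose: "To evaluate the long-term efficacy and safety of the intervention, we will follow up the patients after treatments for 1 month".

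**The concern.** Both arms receive a sudden cervical pull (Step 3: Spinal manipulation). Entry requires negative provocation tests, and the exclusion criteria rule out radiculopathy, myelopathy and neurological disease. New numbness or weakness would therefore be a new sign in a patient screened for its absence, yet neither is named among the adverse events. In the combined arm, patients rise onto their toes while looking upward (Step 1 of the Yijinjing protocol). Two of the three weekly Yijinjing sessions are done at home, and falls are not named either.

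A site that applied the sentence as written would have no duty to report these events, assess their cause or compensate for them, and they would not reach the harm tables. The article's own introduction asks for adverse-event reports on Yijinjing, so a narrow list works against one of the trial's stated reasons.

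**Working it through.** There is no figure in the plan to reproduce on this point. The check is a comparison of texts.

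**1. Is the list open or closed?** The sentence in Safety evaluation joins the term to four items with *are*. It contains no *such as*, *including* or *other*.

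**2. Does any other section widen it?**
- Abstract: says when safety is evaluated, not what counts.
- Dropout criteria: mention adverse reactions and serious adverse events, and define neither.
- Comprehensive suspension criteria: a significant safety problem, not defined.
- Statistical analysis: adverse effects, not defined. That the test uses the Safety evaluation definition is an inference, since no other definition is given.
- Data collection and management: adverse events and safety evaluations are CRF contents, with no definition.
- Quality control: abnormal safety indicators, not defined.
- Follow-up: a safety purpose, with no definition.

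None of them opens the list.

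**3. Which events fall outside the four items as worded?**
- New numbness with no change in pain and no disability: outside.
- Another neurological sign with no change in pain and no disability: outside. New weakness is less clear, because the section sets no threshold for disability and weakness may count under it.
- A fall with no change in pain, syncope, vertigo or disability: outside. A fall followed by even brief pain is inside, because the section sets no minimum duration for a change in pain.

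Numbness appears elsewhere only in Step 2 of the Tuina protocol, as one of the Deqi sensations taken to show that the manipulation is working. That concerns sensation during acupoint pressing, but it gives staff no reason to record numbness as a harm.

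**4. Does the wording also fail in the other direction?** Yes. A change in pain includes a reduction, which is what the primary outcome is meant to show. Taken with the stop rule, the sentence would literally halt treatment in a patient who improves.

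**5. Can the shortfall be sized?** No. The document gives no rate for any adverse event and no share of unlisted events that staff would record anyway. What can be said is how a zero count should be read. If a listed class of event were seen in 0 of 102 patients, all followed, the one-sided 95% upper bound on its rate would be 1 − 0.05^(1/102) = 0.0289, or about 2.9%. For a class outside the definition, applied strictly, the count is zero whatever the true rate, so no such bound can be drawn. This is an illustration, not an estimate of missed events.

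**The case against.** The strongest reply is that nobody would apply the sentence strictly. A strict reading stops treatment for improvement, so the authors probably meant the four items as the events they expected, and the English is loose elsewhere. The same section also has safety monitored at every visit, attending physicians and spine specialists on hand, and a committee of two chief spinal surgeons overseeing a single-centre trial. The CRF lists safety evaluations separately from adverse events. In practice, staff may well record numbness or a fall. A condensed article may also rest on a fuller protocol with a wider definition.

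Much of this stands, and it keeps the priority low. It does not remove the point. The safeguards say who watches and when, not what counts as an event. The article does not leave the definition to another document; it states one. That the sentence cannot be applied as written is a reason to reword it.

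A reader might infer more than the text supports:
- **That all weakness, or falls with brief pain, are excluded.** The section sets no threshold for disability and no duration for pain, so many of these events are covered.
- **That events in home practice go unseen.** The same patients attend Tuina three times a week (24 visits over 8 weeks) and send films of their practice to the teacher.
- **That events in the follow-up month are lost because of the definition.** It is true that "No researcher will supervise them" in that month. But the outcome assessor contacts patients and asks them to attend, although the timing of that contact is ambiguous. Late detection would be a separate matter from what counts as an event.
- **That a number of missed patients can be given.** It would rest wholly on assumed rates.

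**Conclusion.** The point holds as a fault of wording with a safety consequence. The definition is closed as written, no other section opens it, and it leaves out a narrow but relevant residue: numbness or other neurological signs without a change in pain or disability, and falls without any of the four listed items. It also takes in improvement in pain.

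The effect is possible understatement of total harm, of unknown size. It rests on two assumptions: that staff apply the sentence as worded, and that the analysis of adverse effects uses the same definition. If the list is treated as examples, nothing is lost. Tuina is the same in both arms, so a difference between arms could plausibly arise only from exercise-related events. No efficacy conclusion changes. The priority is low, and the correction is cheap.

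**What to change.** Replace the definition in Safety evaluation with wording such as: *any new or worsened sign or symptom during treatment or follow-up, including but not limited to worsened pain, syncope, vertigo, disability, new limb numbness or weakness, and falls (including during home practice); transient Deqi sensations that resolve after the session are not counted*.

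The Deqi exception is needed. Without it, an intended sensation could be logged as an event at any of the planned Tuina sessions (102 patients × 3 per week × 8 weeks = 2,448).

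Revise the stop rule at the same time. Keep the immediate stop for worsened pain, syncope, vertigo and disability, and add new neurological deficit and serious events. Other newly recorded minor events should not trigger an automatic stop. This keeps the present caution for a trial of cervical manipulation while preventing the wider recording definition from halting treatment for trivial complaints.

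The change is two sentences, taken through the ethics committee as Quality control provides. A few more minor events will be listed. Because Trial status says recruitment is under way, events before and after the amendment will have been collected under different wording, and the report should say so.
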